**Fig. 1 Fig1:**
[figure not shown]
Map of study area of cluster randomized controlled trial showing ITN durability assessment clusters. Ten clusters were randomly selected from each study arm

**Fig. 2 Fig2:**
[figure not shown]
Flow chart of trial activities and outputs for monitoring the physical and insecticidal durability of Interceptor G2, Royal Guard and Interceptor in Benin. Two cohorts of nets will be followed per study arm; cohort 1 nets will be assessed for ITN attrition and fabric integrity while cohort 2 nets will be withdrawn (and replaced) and assessed for bioefficacy and chemical content

### Household sensitization and marking of study nets

Households and nets for both cohorts of the durability study will be drawn from the selected clusters of each arm of the cRCT using the ITN distribution list of the trial. Within the first month after ITN distribution, field workers will visit the selected households for each cohort of ITNs to recruit and mark study nets available in them. The number of households enrolled will be increased until the ITN sample size for each cohort is achieved (750 for cohort 1 and 1800 for cohort 2). Using a wash resistant marker, a unique code will be written on the study net to indicate the study arm, cluster ID, household ID and the cohort to which it belongs. During this visit, the durability study will be explained to the householders in their local language and the study team will assist them in hanging up their nets if needed. Only nets which have been successfully hung up and are in use in selected households at the start of the trial will be included in the durability study. GPS coordinates and characteristics of each household (housing type and socio-economic characteristics) included in the durability assessment will also be recorded.

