### Study design

The study area was divided into 60 clusters that were randomly assigned to the three arms of the cRCT using restricted randomization. Study nets are identical in appearance and participating households are blinded to the type of ITN they received. Field data collectors are also blinded to the allocation of households to the study arms. Ten clusters from each study arm have been randomly selected for the durability assessment (Fig. 1). Following ITN distribution, households in these clusters will be visited to mark and prospectively follow 2 separate cohorts of ITNs per arm (Cohorts 1 and 2) every 6–12 months to monitor their physical and insecticidal durability over a period of 36 months. Cohort 1 will consist of at least 750 nets from ~ 250 randomly selected households per arm (assuming 3 ITNs are distributed per household) from 5 study clusters per study arm. These nets will be followed for ITN survivorship and fabric integrity at 6-, 12-, 24- and 36-months post ITN distribution. Cohort 2 will consist of ~ 1800 nets per study arm from ~ 600 households from all 10 randomly selected clusters (60 households per cluster) per study arm to be withdrawn (and replaced with new nets) for assessment of insecticidal activity in laboratory bioassays and experimental hut trials, content of each active ingredient and for other studies. Cohort 1 and cohort 2 nets will receive separate identification numbers and would be sampled from different households to prevent the risk of destructive sampling of nets intended for ITN survivorship studies (cohort 1). Figure 2 provides a summary of the study design and studies to be performed at each timepoint.

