### Follow up surveys for cohort 1 nets

#### Follow-up for ITN attrition

All households in cohort 1 (at least 750 nets/arm) will be visited at 6-, 12-, 24- and 36-months post ITN distribution and nets assessed for attrition at each timepoint by recording the physical presence/absence of each net that was marked in the household. Where a net is not found, the householder will be asked about the reason for the loss of the net, e.g. given away, sold, stolen, worn out and disposed of. Any net which has never been used, will be recorded, and excluded from the analysis. During these surveys, a questionnaire adapted from WHO guidelines will be used to collect data on the number of washes and washing practices for the nets found in each household.

ITN retention may also be affected by householders’ preference of the fabric type used in the formulation of the net. A low preference for polyethylene nets has been previously observed in Benin by the National Malaria Control Programme (NMCP), which may differentially affect the retention of Royal Guard^®^ (polyethylene) compared to Interceptor^®^ and Interceptor^®^ G2 (polyester). As part of these follow up surveys, a short questionnaire will be administered to assess householders’ perception of the ITN fabric types and changes in size of each ITN type to determine whether this may have impacted their decision to discard the net. A subset of ITNs of each type at 0, 12, 24 and 36-months post-distribution (minimum 100 per ITN type) will also be measured to directly examine changes in ITN size over time.

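### The code on each marked net indicates its study arm, which conflicts with the stated blinding of field data collectors and matters chiefly for hole scoring of Interceptor G2 against Interceptor

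*Protocol article*

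**What the plan says.** Under Study design, the article claims two blinds. For householders: "Study nets are identical in appearance and participating households are blinded to the type of ITN they received". For survey staff: "Field data collectors are also blinded to the allocation of households to the study arms".

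Under Household sensitization and marking of study nets, within the first month after distribution "field workers will visit the selected households for each cohort of ITNs to recruit and mark study nets available in them". The marking is permanent ("Using a wash resistant marker") and informative: "a unique code will be written on the study net to indicate the study arm, cluster ID, household ID", together with the net's cohort. The rule covers both cohorts.

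Under Follow-up for ITN attrition, the same code is used at each survey, because attrition is assessed "by recording the physical presence/absence of each net that was marked in the household". For a missing net, "the householder will be asked about the reason for the loss of the net". Under Follow-up for ITN fabric integrity, the survey team drapes each cohort 1 net over a frame and records the number, position and size class of its holes.

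**The concern.** A reader of the Study design section will take the fabric-integrity comparison to be observer-blind. The marking rule puts the arm on the object being scored, where the scorer must look to identify the net.

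Hole counting and sizing leave room for judgement: whether a small tear reaches the lower size limit, which side of a class boundary a hole falls on, and how hard one looks. These counts produce the proportionate hole index categories and the hole-area regression between net types. The recorded reason for loss decides whether a net is excluded from functional survival. If the scorer knows the arm, differences between arms in these outcomes may partly reflect expectation.

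The pair most affected is Interceptor G2 against Interceptor. For those two nets the physical specification gives no obvious clue, so a field blind is achievable and worth protecting.

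**Working it through.** The protocol states no figure to reproduce. The check sets the statements side by side, with simple counts to show reach.

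1. **Who is said to be blind.** Study design names households and field data collectors. It claims no blind for laboratory staff.

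2. **What is on the net.** The marking section lists four elements: arm, cluster, household and cohort. It mentions no neutral symbol, no withheld key, and no separation between those who mark and those who later score.

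3. **When the code is seen.** Identifying the marked net requires reading the code. Hole scoring follows with that net in hand at 6, 12, 24 and 36 months, so exposure to the code is part of the procedure.

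4. **How many nets.** Marked per arm: at least 750 (cohort 1) + about 1800 (cohort 2) = 2550; over three arms, 3 × 2550 = 7650. Routine hole scoring concerns cohort 1, so the Interceptor G2 and Interceptor pair starts with 2 × 750 = 1500 nets. Cohort 2 can also enter: the fabric-integrity section draws on destructively sampled nets if fewer than 250 are available. With the 70% three-year control-arm attrition assumed under Sample size calculations, 750 × (1 − 0.70) = 225 nets would remain at 36 months, 25 short of 250. On that assumption, coded cohort 2 nets would also be scored.

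5. **Which comparison depends on the code.** Under Study arms, Interceptor and Interceptor G2 are both blue, rectangular, 100-denier polyester and 1.8 m in each dimension. Royal Guard is polyethylene and 1.6 m high. The code is therefore the clearest route to unblinding the first pair. For Royal Guard, fabric and height can reveal the product without it.

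6. **Would a neutral arm symbol repair this?** Only partly. Every net in a cluster has the same product. Without an arm element, learning the product of one net reveals one cluster. With an arm symbol, it reveals every cluster bearing that symbol: 5 per arm for cohort 1, 10 per arm over both cohorts. If Royal Guard is recognised by its fabric, two symbols remain, and decoding either one decodes the other.

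7. **Is the arm element needed?** No. Clusters were randomised, so the cluster ID and the allocation list give the arm at analysis.

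**The case against.** The strongest reply is that the text says the code indicates the arm, not that it spells out the product. A masked symbol would be compatible with blinded collectors, and custody of the key is a detail that an article may leave to the full protocol. This stands in part: the document does not prove that any collector knew the arm. A reader might infer that the blind was in fact broken at every survey, but the text supports only a conflict as written. Masking is one possible reading, and it would still group the nets by arm.

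Reason for loss is the householder's report, and the article calls householders blinded. That stands, and is why this outcome is secondary; the collector's questioning and coding are the only route for bias. Hole sizes fall in fixed centimetre classes, which limits judgement without removing it. Presence or absence of a net is fairly objective.

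A reader might extend the point to the laboratory. The document does not support this. It claims no laboratory blind, and Table 2 gives each brand its own strain and assay, so staff must know the brand. Laboratory ovary staging of field nets concerns only Royal Guard, against unexposed controls.

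A reader might also size the bias by assuming that a share of nets is misgraded and setting it against the 9.4-point detectable difference. That figure refers to attrition, not to hole grade or functional survival, and the document gives no basis for the assumed share.

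Finally, published 24-month results of the parent trial might be thought to have coloured all the scoring. Under Status of study, surveys to 24 months were already complete at publication, so this argument bears mainly on the 36-month round.

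**Conclusion.** The concern holds in a limited form. The blinding statement for field data collectors and the net-marking rule cannot both be taken at face value. The conflict covers every net marked for cohorts 1 and 2, not every net distributed in the parent trial. Its main consequence is possible observer bias in hole scoring of Interceptor G2 against Interceptor, and to a lesser degree in how reported reasons for loss are recorded. Neither the direction nor the size of a bias can be established.

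The conclusion assumes that the arm element is readable, or can be decoded, by the survey team. If it was masked and the key withheld throughout, the problem shrinks to a code that groups nets by arm, and the article should say so. The point is worth acting on because the arm element serves no purpose that the cluster ID does not already serve.

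**What to change.** Change the marking rule so that the code is an arm-free serial number, with the serial-to-arm link held only by the data manager.

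Marking followed the 2020 distribution, so nets already coded need a different remedy. For the 36-month survey, keep the arm key from those who score holes, or cover the arm element before scoring where practicable. Apply the same step to any cohort 2 nets examined to reach the minimum of 250.

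Amend the blinding statement under Study design to say which outcomes and survey rounds were not assessed blind where the code revealed the arm. If the arm element was masked, say so and state who held the key.

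The cost is a link file, a small handling step at the 36-month survey and a less favourable blinding statement for completed rounds. Sample size and analysis models do not change.

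### Cohort 1 attrition is measured only on nets hung and in use at a visit up to a month after distribution, so earlier losses, which may differ by fabric, cannot count

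*Protocol article*

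**What the plan says.** All references are to the protocol article.

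- **Timing and entry** (Methods, Household sensitization and marking of study nets). Households are drawn from the trial's distribution list. "Within the first month after ITN distribution, field workers will visit the selected households" to recruit and mark nets. On entry: "Only nets which have been successfully hung up and are in use in selected households at the start of the trial will be included". At that visit "the study team will assist them in hanging up their nets if needed".
- **Top-up** (same section). "The number of households enrolled will be increased until the ITN sample size for each cohort is achieved", which for cohort 1 means 750 nets per arm.
- **Outcome** (Follow-up for ITN attrition). Attrition is assessed by "recording the physical presence/absence of each net that was marked in the household", at 6, 12, 24 and 36 months counted from distribution. In addition: "Any net which has never been used, will be recorded, and excluded from the analysis".
- **Expected difference by fabric** (same section). "A low preference for polyethylene nets has been previously observed in Benin", and the article adds that this may affect retention of Royal Guard (polyethylene) differently from the two polyester nets.
- **Objectives** (Study objectives). The first covers survivorship, attrition and fabric integrity over three years of household use. The third covers fabric preference and its impact on retention.
- **Functional survival** (Statistical analysis). Nets given away, sold or stolen are left out.

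**The concern.** Clusters were randomised, but the marked nets are a subset chosen after allocation, and the choice depends on whether the household had accepted the net. Acceptance is what the third objective studies, and the article expects it may differ by fabric. Because enrolment continues until each arm has 750 nets, the cohort sizes would not reveal an arm that lost more nets before marking.

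Attrition is also the survival outcome that has to show disposal through dislike, since functional survival leaves out nets given away, sold or stolen. If its denominator is filtered by early acceptance, the Royal Guard comparison could look more favourable than a count from distribution would. The Discussion intends the attrition results for replacement planning and procurement, where the nets issued are the natural base.

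**Working it through.** **The plan's own figures.** The documents give no first-month loss for any arm, so there is no figure to reproduce. Two numbers from Sample size calculations serve as a scale: 70% control-arm attrition over three years, and a detectable difference of 9.4 points over that period. The calculation below does not depend on how those were derived.

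**What happens to each kind of net**

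| Status at the marking visit | Enters cohort 1? | Counted as attrition? |
|---|---|---|
| Already given away, sold or discarded | No | No |
| Present, still refused after hanging help | No | No, and no later follow-up |
| Present but unhung, then hung with help and used | Yes | Yes, if lost later |
| Hung and in use | Yes | Yes, if lost later |

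The first two rows are the gap. The later exclusion of never-used nets should affect few nets, because entry requires use. It matters only if the entry condition was applied loosely, for example to a net hung with help and then never slept under. Its direction is not fixed: dropping such a net while it is still in the house raises measured attrition, and dropping one that has since gone lowers it.

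**Formula.** Let *e* be the share of issued nets gone before marking and *a* the attrition among marked nets at a given time.

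Attrition from distribution = *e* + (1 − *e*) × *a*

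If *a* is the same in both arms, the planned analysis shows a difference of zero, while the difference from distribution is

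hidden gap = (*e* for Royal Guard − *e* for polyester) × (1 − *a*)

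**Assumed inputs (not in the documents).** *e* = 5–15% for Royal Guard and 2–3% for polyester. The difference in *e* then runs from 5 − 3 = 2 points to 15 − 2 = 13 points.

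**At 36 months, *a* = 70%**

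- Low end: polyester 0.03 + 0.97 × 0.70 = 70.9%; Royal Guard 0.05 + 0.95 × 0.70 = 71.5%; gap 0.6 points.
- High end: polyester 0.02 + 0.98 × 0.70 = 70.6%; Royal Guard 0.15 + 0.85 × 0.70 = 74.5%; gap 3.9 points.

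**Earlier, when 80% of marked nets survive**

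- Low end: 0.02 × 0.80 = 1.6 points.
- High end: 0.13 × 0.80 = 10.4 points.

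Under a constant hazard that gives 70% attrition at 36 months, attrition is about 18% at 6 months (1 − 0.30^(6/36)), so the 80% case is close to the first survey.

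**Plausibility of the upper end.** The same constant hazard implies 1 − 0.30^(1/36) = 3.3% loss in one month. A 15% first-month loss is about 4.5 times that (15 / 3.3), so it would need marked early rejection.

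**The case against.** The case for leaving the plan as it is has several sound parts.

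- **The objectives speak of household use.** A cohort of nets hung and in use fits that wording, and it is the right set for fabric integrity. This stands in part. It is weaker for a question about how fabric preference affects retention, and the survey clock runs from distribution.
- **Stored nets are not simply lost.** The team helps to hang nets, so an unhung net still in the house can be enrolled. This stands. The exclusion is confined to nets already gone or still refused, within at most one month of 36.
- **Later rejection is still measured.** Each survey records reasons for loss, and a questionnaire asks about fabric and size in the decision to discard. This stands. A reader might infer that fabric rejection drops out of the third objective altogether. The article does not support that, because only rejection before marking is missed.
- **No bias is demonstrated.** A reader might infer that Royal Guard attrition is understated as a matter of fact. The article says only that preference may affect retention, and gives neither timing nor size. If early loss is similar across arms, the hidden gap is nil.
- **The largest figures should not be set against 9.4 points.** That difference is specified over three years. The 10.4-point figure belongs to an earlier time, for which no target is stated. At 36 months the upper end is 3.9 / 9.4, or about 41% of it.
- **The top-up is not a one-for-one swap.** It adds households, and it also covers households with fewer than the assumed three nets. This is correct, but it does not restore nets lost before marking to the denominator.

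**Conclusion.** The planned attrition and retention comparison is conditional on a net having been accepted and in use at a visit up to a month after distribution. That follows directly from the text. Whether the comparison between arms is biased depends on early loss differing by fabric, which the article treats as possible but does not quantify. If polyethylene is rejected earlier, Royal Guard attrition from distribution and the fabric effect on retention could be understated.

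Under the assumed 5–15% against 2–3% early loss and equal survival afterwards, the understatement is about 0.6 to 3.9 points at 36 months. It is larger near the start of the curve: 1.6 to 10.4 points at 80% survival. The effect on the three-year result is modest, but it bears directly on the third objective, and the plan as described would not show whether it occurred. The hung-and-used set remains appropriate for fabric integrity and functional survival.

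**What to change.** Nets were distributed in 2020 and surveys are complete to 24 months (Status of study), so recruitment cannot be redone. The change is to analysis and reporting.

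1. For the visited cohort 1 households, use the distribution list to tabulate by arm the nets issued, found at the marking visit, and marked.
2. Add an attrition and retention analysis from the distribution date, in which issued nets already gone at the marking visit count as attrition. Show it beside the planned marked-net analysis.
3. Keep marked nets later found never used in the retention analysis, as retained but unused.
4. Treat issued nets that were present but unmarked as having unknown later status, because they carry no code and have no planned follow-up. Censor them, or give bounds: if they are a share *u* of issued nets, attrition from distribution is uncertain by up to *u*.
5. Keep the hung-and-used set for fabric integrity and functional survival, and describe the planned curves as conditional on initial use.

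**Cost.** No new fieldwork if the records exist. Reasons for loss before marking may be missing, and distribution or marking-visit records may be incomplete. In that case, report issued against marked nets per visited household by arm and state the limitation. Overall attrition will look slightly higher.

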### Follow up surveys for cohort 1 nets

#### Follow-up for ITN attrition

All households in cohort 1 (at least 750 nets/arm) will be visited at 6-, 12-, 24- and 36-months post ITN distribution and nets assessed for attrition at each timepoint by recording the physical presence/absence of each net that was marked in the household. Where a net is not found, the householder will be asked about the reason for the loss of the net, e.g. given away, sold, stolen, worn out and disposed of. Any net which has never been used, will be recorded, and excluded from the analysis. During these surveys, a questionnaire adapted from WHO guidelines will be used to collect data on the number of washes and washing practices for the nets found in each household.

ITN retention may also be affected by householders’ preference of the fabric type used in the formulation of the net. A low preference for polyethylene nets has been previously observed in Benin by the National Malaria Control Programme (NMCP), which may differentially affect the retention of Royal Guard^®^ (polyethylene) compared to Interceptor^®^ and Interceptor^®^ G2 (polyester). As part of these follow up surveys, a short questionnaire will be administered to assess householders’ perception of the ITN fabric types and changes in size of each ITN type to determine whether this may have impacted their decision to discard the net. A subset of ITNs of each type at 0, 12, 24 and 36-months post-distribution (minimum 100 per ITN type) will also be measured to directly examine changes in ITN size over time.

#### Follow-up for ITN fabric integrity

Fabric integrity (hole index) and condition will be observed on all nets of cohort 1 at 6-, 12-, 24- and 36-months post distribution. Where the minimum number (250) of nets for fabric integrity is not attainable from the longitudinal cohort (cohort 1) due to loss, ITNs sampled destructively from the same clusters for bio-efficacy would first be examined for fabric integrity prior to the bio-efficacy studies. The survey team will inspect the nets outside in broad day light to determine the hole index using a portable frame over which the net can be draped during inspection. The nets will be returned to the family right after the inspection. Hole number, position and size will be assessed on each ITN panel (roof and sides) using hole assessment sheets and classified into 4 sizes (size 1: 0.5-2 cm, Size 2: 2–10 cm, Size 3: 10-25 cm, and size 4: > 25 cm). Physical integrity will be measured as the proportionate hole index (pHI), categorized based on recommended cut-off points into “good” condition (pHI 0–64), “acceptable” condition (pHI 65–642) and “torn” (pHI 643 +) defined in WHO guidelines [13].

